### 1.3. Study Design

[figure not shown]

| Overview of Study Design and Key Features      |                                                                                                                                                                                                                                                                                                                                                                                                                                                                                                                                                                                                                                                                                                                                                                                                                                                       |
|------------------------------------------------|-------------------------------------------------------------------------------------------------------------------------------------------------------------------------------------------------------------------------------------------------------------------------------------------------------------------------------------------------------------------------------------------------------------------------------------------------------------------------------------------------------------------------------------------------------------------------------------------------------------------------------------------------------------------------------------------------------------------------------------------------------------------------------------------------------------------------------------------------------|
| Data and Safety Monitoring Board (DSMB) | 
 
• An independent data and safety monitoring board (DSMB) will be established to regularly review and analyze all safety data.
 
• The efficacy data generated from the study will be evaluated by the DSMB for potential risks and benefits.
 
• DSMB will review the serious adverse events continuously. The DSMB will review data such as frequency and severity of all adverse events and demographics.
 
• Specific meetings may be held during the study for any safety concerns.
 
• The DSMB will give recommendations on whether the study should be continued, adjusted, or terminated based on the results of the data review if any study termination criteria is met. Other responsibilities and details of the DSMB will be included in the DSMB Charter.
 
 |

## 2. Statistical Hypotheses

Null hypothesis (H0): The success rate of cerebral angiography via TRA approach is inferior to that via TFA approach (i.e. the difference in success rates  $\leq -5\%$ );

Alternative hypothesis (H1): The success rate of cerebral angiography via TRA is not inferior to that via TFA (i.e. the difference in success rates  $> -5\%$ ).

The Wald Z test will be used for comparison between groups at one-sided significance level of 0.025. If  $p < 0.025$ , the null hypothesis H0 is rejected, supporting the conclusion that the success rate of cerebral angiography via TRA approach is not inferior to that via TFA approach.

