## 4. Planned Analyses

### 4.1. Interim Analyses

An independent data and safety monitoring board (DSMB) will be established to regularly review and analyze all safety data and/or efficacy data for the evaluation of potential risks and benefits. Other responsibilities and details of the DSMB will be included in the DSMB Charter.

An interim analysis will be conducted by the DSMB after the 30-day follow-up of 430 participants. The Haybittle-Peto method will be used to control the overall Type I error rate: the p-value boundary for the one-sided test at the interim analysis will be set at 0.001, and the p-value boundary for the one-sided test at the final analysis will be set at 0.024.

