#### Rate difference and 95% CI calculation sample code:

```
PROC FREQ DATA=adeff;
    TABLE TRTPN*AVAL / RISKDIFF(CL=WALD) ALPHA=0.05;
    WEIGHT COUNT/zeros;
    ODS OUTPUT PDIFFCLS = diff;
RUN;
```

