#### Wald test for non-inferiority sample code:

```
PROC FREQ DATA=adeff;
    TABLE TRTPN*AVAL / RISKDIFF(NOINF MARGIN=.05) ALPHA=0.025;
    WEIGHT COUNT/zeros;
    ODS OUTPUT PdiffNoninf=noninf;
RUN;
```

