## 11. Multiplicity

Not applicable.

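### The SAP states two final success thresholds, one-sided 0.025 in Section 2 and 0.024 in Section 4.1; the numerical effect is small, but the primary decision rule should be aligned

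*Combined protocol and SAP*

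**What the plan says.** **The 0.025 rule.** SAP Section 2: "The Wald Z test will be used for comparison between groups at one-sided significance level of 0.025". The next sentence rejects H0 and concludes non-inferiority if p < 0.025, without mentioning an interim. Protocol 7.2 has the same rule for its chi-square test.

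**The 0.024 rule.** SAP Section 4.1: "An interim analysis will be conducted by the DSMB after the 30-day follow-up of 430 participants". It continues: "The Haybittle-Peto method will be used to control the overall Type I error rate". The one-sided interim boundary is given as 0.001. For the end of the trial the text reads: "the p-value boundary for the one-sided test at the final analysis will be set at 0.024".

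**What the rest of the SAP follows.**
- Section 8.1.2.2.2 presents the rate difference with a 95% Wald interval, and the sample code for it uses "RISKDIFF(CL=WALD) ALPHA=0.05".
- The sample code for the non-inferiority test uses "RISKDIFF(NOINF MARGIN=.05) ALPHA=0.025".
- Section 11, Multiplicity, reads in full "Not applicable".
- Section 1.1 says that Table 1 outlines any changes from the protocol's analysis. Table 1 lists the move to Wald methods and to the risk ratio, but neither the interim nor the 0.024 boundary.

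The protocol's statistical section plans no interim analysis. Protocol 11.5 lets the DSMB evaluate efficacy data and recommend termination, but sets no boundary.

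**The concern.** A confirmatory SAP should give one success rule for its single primary hypothesis. This one gives two. A final one-sided p from 0.024 up to 0.025 would establish non-inferiority under Section 2 and fail under Section 4.1, and no sentence says which governs. If the result fell there, the choice would be made with the data in view.

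The reported interval would not settle it. A two-sided 95% interval corresponds to one-sided 0.025, so its lower limit can lie above -5% when the 0.024 rule is not met. Table 1 gives agreement between interval and test as the reason for moving to Wald methods, and a 95% interval beside a 0.024 boundary undoes that agreement.

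**Working it through.** **Inputs.** Section 2 level 0.025; Section 4.1 boundaries 0.001 and 0.024; interim at 430 participants; 858 enrolled, 429 per arm; drop-out 10%, so 429 × 0.9 = 386 evaluable per arm and 2 × 386 = 772 in total; success rates 97% (TRA) and 98% (TFA); margin -5% (SAP Sections 2, 3 and 4.1).

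**1. The plan's own split.** 0.001 + 0.024 = 0.025, so Section 4.1 divides the level that Section 2 uses in full. With Section 2's level at the end, the simple sum is 0.001 + 0.025 = 0.026.

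**2. Overall error allowing for correlation.** In large samples the interim and final Z statistics are bivariate normal with correlation √(430/858) = 0.708. Overall error = α₁ + α₂ − P(both crossed). The critical values are 3.090 for 0.001, 1.960 for 0.025 and 1.977 for 0.024.
- Section 2 at the end: 0.001 + 0.025 − 0.00072 = 0.0253.
- Section 4.1 at the end: 0.001 + 0.024 − 0.00071 = 0.0243.

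If the information fraction is 430/772, these become 0.0252 and 0.0242. At 430/858, the largest final level that keeps the total at 0.025 is about 0.0247, so 0.024 is slightly conservative and 0.025 slightly too liberal.

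**3. Matching interval.** 1 − 2 × 0.024 = 0.952, a two-sided 95.2% interval (z = 1.977).

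**4. Can a result fall in the gap?** The Wald statistic is Z = (p_TRA − p_TFA + 0.05)/SE, with SE² = p_TRA(1 − p_TRA)/n + p_TFA(1 − p_TFA)/n.
- 429 per arm, 18 TRA and 6 TFA failures: rates 0.9580 and 0.9860, difference -0.0280, SE 0.01122, Z = 1.964, p = 0.0248. The 95% lower limit is -4.996% (success); the 95.2% lower limit is -5.015% (failure).
- 386 per arm, 24 TRA and 17 TFA failures: p = 0.0241, lower limits -4.975% and -5.003%, the same split.

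**5. How likely is it?** The Wald test was enumerated exactly at 97% and 98%, for 375 to 429 per arm with equal or near-equal arms. The probability of a final p in the gap averages about 0.2%, with a maximum of 0.9%. At 386 per arm it is essentially zero (0.00006%). At 429 per arm it is 95.5% − 95.0%, about 0.5%. This probability is also the power lost at the final analysis by using 0.024.

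**6. What alignment does not do.** With true rates on the margin (93% and 98%) and 386 per arm, the exact size of the final Wald test alone is 0.0318 at nominal 0.025 and 0.0317 at nominal 0.024.

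**The case against.** The strongest reply is that a sensible reading exists. Section 4.1 is the more specific text: it names the final analysis, states its purpose, and its two boundaries add to 0.025. Section 2 repeats protocol 7.2 closely and could be taken as the overall level. This largely stands. A reader might infer that the plan has no usable success rule; it has one, in Section 4.1. But Section 2 gives an explicit rejection rule at p < 0.025, not just an overall level, so the conflict in the text remains.

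The supporting items are also weaker individually than together. Section 11 may have been written with multiple endpoints in mind. The code is labelled as sample code, and ALPHA in the non-inferiority call sets the displayed limits, not the p-value. No sentence makes the 95% interval the success criterion, and reporting one as a description beside a slightly adjusted final level is acceptable. These points show that the 0.024 boundary was not carried through; they are not separate decision rules.

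A reader might infer a serious inflation of type I error. The figures do not support that: the excess over 0.025 is about 0.0003. The interim is a real opportunity to cross (39% by exact Wald calculation at the design rates with 215 per arm), but this does not enlarge the difference between 0.024 and 0.025.

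A reader might also infer that adopting 0.024 secures 0.025 for the test actually planned. It does so only in large samples; step 6 shows a size of about 0.032 at either level.

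Nor was efficacy review wholly absent from the protocol. What its text lacks is a formal interim with boundaries. The DSMB Charter, to which Section 4.1 refers, may say more but is not among the documents.

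**Conclusion.** The point holds as an inconsistency in the primary decision rule. Sections 2 and 4.1 differ for a final p from 0.024 up to 0.025, and the interval, the sample code, Section 11 and Table 1 do not carry the interim through. The effect is small: overall one-sided error of about 0.0253 against 0.0243, and a chance of about 0.2% on average (at most 0.9%) of landing where the rules differ.

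The error figures assume large-sample normality, an information fraction near one half, and that crossing 0.001 at the interim counts as success. The gap probabilities assume 97% and 98% and the Wald test. The case for correction rests on having one pre-specified rule at little cost. The Wald test's finite-sample size is a separate issue, and its error is much larger than the one described here.

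**What to change.** Before final results are known:
- **SAP Section 2:** state that H0 is rejected if the one-sided p is below 0.001 at the interim or below 0.024 at the final analysis.
- **SAP Sections 8.1.2.2.2 and 8.1.2.3.1:** show a 95.2% interval for the rate difference as the one that matches the decision, with `ALPHA=0.048` in the confidence-limit call and `ALPHA=0.024` in the non-inferiority call. The 95% interval may stay, labelled descriptive.
- **SAP Section 11:** refer to the 0.001 and 0.024 split in Section 4.1.
- **SAP Table 1:** add the interim and its boundaries as a change from the protocol, with the reason.

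The cost is wording and two ALPHA values. By exact Wald calculation, final power stays at 93.0% with 386 per arm, goes from 95.5% to 95.0% with 429 per arm, and falls by at most 0.9 points over the sizes examined. No change in sample size is needed. These edits align the nominal rules only and do not correct the size of the Wald test.

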## 3. Sample Size Considerations

This study will test the hypothesis that the success rate of diagnostic cerebral angiography by TRA approach is not inferior to that by TFA approach.

The success rates of diagnostic cerebral angiography by TRA and TFA are assumed to be 97% and 98% respectively. With a margin for non-inferiority of -5% and a drop-out rate of 10%, 429 cases are needed for each group to achieve a power of 90% at one-sided significance level of

0.025, according to PASS 15 software, and thus a total of 858 subjects need to be enrolled in this study.

## 4. Planned Analyses

### 4.1. Interim Analyses

An independent data and safety monitoring board (DSMB) will be established to regularly review and analyze all safety data and/or efficacy data for the evaluation of potential risks and benefits. Other responsibilities and details of the DSMB will be included in the DSMB Charter.

An interim analysis will be conducted by the DSMB after the 30-day follow-up of 430 participants. The Haybittle-Peto method will be used to control the overall Type I error rate: the p-value boundary for the one-sided test at the interim analysis will be set at 0.001, and the p-value boundary for the one-sided test at the final analysis will be set at 0.024.

### 4.2. Final Analyses

The final planned primary analyses will be performed after the completion of the following sequential steps:

1. All subjects have completed or discontinued the study as defined in the protocol.
2. All required database cleaning activities have been completed and database freeze has been declared by Data Management.
3. Final database release.
4. Randomisation codes have been distributed according to SOP.

## 5. Analysis Sets

| Population              | Definition / Criteria                                                                                                                                                                     | Analyses Evaluated                                                                      |
|-------------------------|-------------------------------------------------------------------------------------------------------------------------------------------------------------------------------------------|-----------------------------------------------------------------------------------------|
| Full Analysis Set (FAS) | 
 
The FAS will include subjects randomized to receive TRA or TFA cerebral angiography, with recorded evaluation results of the diagnosis.
 
 | 
 
Population analyses
 
Efficacy
 
 |

| Population             | Definition / Criteria                                                                                                                                                                                                                                                                                                                                                                                                                                                                                                                                                                      | Analyses Evaluated                                         |
|------------------------|--------------------------------------------------------------------------------------------------------------------------------------------------------------------------------------------------------------------------------------------------------------------------------------------------------------------------------------------------------------------------------------------------------------------------------------------------------------------------------------------------------------------------------------------------------------------------------------------|------------------------------------------------------------|
|                        | 
 
Statistical analysis will be performed according to the intervention group randomly assigned (regardless of the actual intervention received).
 
The FAS is the main set for the efficacy analysis of this study.
 
                                                                                                                                                                                                                                                                                                                 |                                                            |
| Safety Set (SS)        | 
 
The SS will include all subjects randomized and received cerebral angiography via TRA approach or TFA approach.
 
This analysis will be performed according to the actual intervention received.
 
                                                                                                                                                                                                                                                                                                                                  | 
 
Safety
 
   |
| Per Protocol Set (PPS) | 
 
PPS is a subset of the FAS, including subjects from the FAS with no major protocol deviations.
 
The criteria for major protocol deviations should be finalized before the lock of the database, and the lists of subjects to be included and excluded from the PPS should be reviewed and discussed by the principal investigator, the statistician, and the sponsor at the data review meeting before the lock of the database.
 
PPS-based analyses will serve as supportive analyses to complement FAS-based analyses.
 
 | 
 
Efficacy
 
 |

## 5.1. Protocol Deviations

- Major protocol deviations will be summarised and all protocol deviations will be listed by subject.
- Major deviations which result in exclusion from the PPS will also be summarised and listed.
- Protocol deviations will be tracked by the study team throughout the conduct of the study in accordance with the Medical Monitoring Plan.
  - Data will be reviewed prior to freezing the database to ensure all major deviations and deviations which may lead to exclusion from the analysis are captured and categorized on the protocol deviations dataset.

## 6. Considerations for Data Analyses and Data Handling Conventions

All statistical analyses will be performed by SAS ® system 9.4 (or higher version). Tables, figures and listings will be generated as RTF files.

Study population analyses, efficacy analyses and safety analyses will be performed by intervention groups, which will be represented by ‘Transradial Access’ and ‘Transfemoral Access’.

Unless otherwise specified, categorical variables will be summarized by number (n) and percentages (%) of subjects under each category, as well as number and percentages of subjects with missing categories. Continuous variables will be summarized by number of non-missing subjects (n), arithmetic mean, standard deviation (SD), median, minimum, and maximum.

Table 2 provides an overview of appendices within the SAP for outlining general considerations for data analyses and data handling conventions.

**Table 2 Overview of Appendices**

| Component                                                    |
|--------------------------------------------------------------|
| Appendix 1: Visit and Analysis Windows                       |
| Appendix 2: Data Display Standards & Handling Conventions    |
| Appendix 3: Premature Withdrawals & Handling of Missing Data |
| Appendix 4: Listing of Abbreviations                         |

## 7. Study Population Analyses

### 7.1. Overview of Planned Study Population Analyses

The study population analyses will be based on the FAS population, unless otherwise specified.

Table 3 provides an overview of the planned study population analyses.

**Table 3 Overview of Planned Study Population Analyses**

|                                                                                                                                                                           | Data Displays Generated |        |         |  |   |
|---------------------------------------------------------------------------------------------------------------------------------------------------------------------------|-------------------------|--------|---------|--|---|
|                                                                                                                                                                           | Table                   | Figure | Listing |  |   |
| Subject Disposition                                                                                                                                                       |                         |        |         |  |   |
| Number of subjects screened                                                                                                                                               |                         |        |         |  |   |
| Subjects discontinued prior to randomization 

– Screen failure and reasons

– Withdrawal by subject

– Other

 |                         |        |         |  |   |
| Randomized subjects                                                                                                                                                       |                         |        |         |  |   |
| Subjects who received cerebral angiography                                                                                                                                |                         |        |         |  |   |
| Subjects who did not receive cerebral angiography and reasons                                                                                                             |                         |        |         |  |   |
| Subjects who completed the study                                                                                                                                          |                         |        |         |  |   |
| Subjects who discontinued from the study prematurely and primary reasons                                                                                                  |                         |        |         |  |   |
| Full Analysis Set                                                                                                                                                         |                         |        |         |  |   |
| Safety Set                                                                                                                                                                |                         |        |         |  |   |
| Per Protocol Set                                                                                                                                                          |                         |        |         |  |   |
| Demographics and Baseline Characteristics                                                                                                                                 |                         |        |         |  |   |
| Sex                                                                                                                                                                       |                         | Y      |         |  | Y |

|                                                                                                                                | Data Displays Generated |        |         |
|--------------------------------------------------------------------------------------------------------------------------------|-------------------------|--------|---------|
|                                                                                                                                | Table                   | Figure | Listing |
| Age (years)                                                                                                                    |                         |        |         |
| Race                                                                                                                           |                         |        |         |
| Baseline body weight (kg)                                                                                                      |                         |        |         |
| Body height (cm)                                                                                                               |                         |        |         |
| Baseline BMI (kg/m  )                                                                                              |                         |        |         |
| Modified Rankin Scale (mRS) score                                                                                              |                         |        |         |
| Smoking history                                                                                                                |                         |        |         |
| Alcohol history                                                                                                                |                         |        |         |
| Prior Medical History                                                                                                          |                         |        |         |
| Diabetes (Yes/ No/ Unknown)                                                                                                    | Y                       |        | Y       |
| Type of Diabetes (Type I/ Type II/ Other)                                                                                      |                         |        |         |
| Hypertension (Yes/ No/ Unknown)                                                                                                |                         |        |         |
| Hyperlipidemia (Yes/ No/ Unknown)                                                                                              |                         |        |         |
| Coronary Heart Disease (Yes/ No/ Unknown)                                                                                      |                         |        |         |
| Type of Coronary Heart Disease (Acute Myocardial Infarction /Old Myocardial Infarction /Unstable Angina/ Stable Angina/ Other) |                         |        |         |
| Cerebrovascular Disease (Yes/ No/ Unknown)                                                                                     |                         |        |         |
| Type of Cerebrovascular Disease (Ischemic/ Hemorrhagic/ Mixed/ Other)                                                          |                         |        |         |
| Puncture History (Yes/ No/ Unknown)                                                                                            |                         |        |         |

|                                                                                                                              | Data Displays Generated |        |         |
|------------------------------------------------------------------------------------------------------------------------------|-------------------------|--------|---------|
|                                                                                                                              | Table                   | Figure | Listing |
| Puncture Site ( Left Radial Artery/ Right Radial Artery/ Left Femoral Artery/ Right Femoral Artery/ Other)                   |                         |        |         |
| Purpose of Puncture (Cerebrovascular Intervention/ Cardiovascular Intervention/ Other)                                       |                         |        |         |
| Aortic Surgery History (Yes/ No/ Unknown)                                                                                    |                         |        |         |
| Puncture sites of aortic surgery (left radial artery/ right radial artery/ left femoral artery/ right femoral artery/ other) |                         |        |         |
| Allergy History (Yes/ No/ Unknown)                                                                                           |                         |        |         |
| Current Admission Diagnosis                                                                                           |                         |        |         |
| Current Admission Diagnosis: SOC and PT                                                                                      | Y                       |        | Y       |
| Pre-Operation Imaging Examination                                                                                     |                         |        |         |
| Left Radial Artery Diameter (mm)                                                                                             | Y                       |        | Y       |
| Right Radial Artery Diameter (mm)                                                                                            |                         |        |         |
| Left Femoral Artery Diameter (mm)                                                                                            |                         |        |         |
| Right Femoral Artery Diameter (mm)                                                                                           |                         |        |         |
| Left Radial Artery Growth Status (Normal/Abnormal)                                                                           |                         |        |         |
| Left Radial Artery Abnormal Category                                                                                         |                         |        |         |
| Right Radial Artery Growth Status (Normal/Abnormal)                                                                          |                         |        |         |
| Right Radial Artery Abnormal Category                                                                                        |                         |        |         |
| Concomitant Medications                                                                                               |                         |        |         |

|                                                | Data Displays Generated |        |         |
|------------------------------------------------|-------------------------|--------|---------|
|                                                | Table                   | Figure | Listing |
| Concomitant Medications by ATC[level 3] and PN | Y                       |        | Y       |

